## **LIST OF ABBREVIATIONS AND RELEVANT DEFINITIONS**

|             |                                                                                                     |
|-------------|-----------------------------------------------------------------------------------------------------|
| aTOS | Arterial thoracic outlet syndrome                                                            |
| AVG  | Algemene Verordening Gegevensbescherming                                                     |
| CDT  | Catheter direct thrombolysis                                                                 |
| DOAC | Direct oral anticoagulants                                                                   |
| ERN  | European Reference Networks                                                                  |
| IC   | Informed Consent                                                                             |
| nTOS | Neurogenic thoracic outlet syndrome                                                          |
| PIF  | Patient information form                                                                     |
| PTA  | Percutaneous transluminal angioplasty                                                        |
| RCT  | Randomized controlled trials                                                                 |
| TOD  | Thoracic outlet decompression                                                                |
| TOS  | Thoracic outlet syndrome                                                                     |
| UMCU | University Medical Centre Utrecht                                                            |
| vTOS | Venous thoracic outlet syndrome                                                              |
| WGBO | Law on medical treatment agreement (in Dutch: Wet op Geneeskundige BehandelingsOvereenkomst) |

## SUMMARY

**Rationale:** Thoracic outlet syndrome (TOS) is a rare disease that is caused by compression of the neurovascular bundle in the thoracic outlet region. Based on the compressed structure we can distinguish three types of TOS; from most common to least common these are neurogenic (nTOS), venous (vTOS) and arterial (aTOS). TOS can be treated conservatively through physical therapy and/or anticoagulation therapy with direct oral anticoagulants (DOAC), or invasively with thoracic outlet decompression surgery (TOD) where the first rib is routinely removed. In a- and vTOS patients additional therapy can consist of medical or mechanical thrombus removal and surgical interventions to restore vascular patency such as thrombolysis, stenting, percutaneous transluminal angioplasty or a surgical bypass. Due to the low incidence and the lack of high quality data on all three TOS forms but especially vTOS and aTOS, little is known on the optimal treatment of these patients.

Creating an ongoing registry that supports collective prospective patient data gathering and sharing is a proven method to perform research on medical disorders presenting with a very low incidence. This registry is an online registry for data collection on all patients with TOS.

**Objective:** To collect clinical data that can be used for future research on optimising diagnostic protocols and treatment strategies, treatment safety, symptom-free survival, quality of life, and functional disability among all three forms of TOS patients.

**Registry design:** This is a longitudinal observational monocenter registry.

**Registry population:** All adult patients diagnosed with aTOS, nTOS or vTOS who are currently being treated or have been treated in the University Medical Centre Utrecht (UMCU) are eligible for inclusion. In addition, patients with a primary upper extremity deep venous thrombosis without a clear vTOS compression will also be included.

**Main parameters/endpoints:** Data will be collected for future research of which the exact research question is not known at this time. When new research will be conducted, study parameters will be set. A new study application has to be submitted to the METC.

**Nature and extent of the burden and risks associated with participation, benefit and group relatedness:** The burden for patients to participate in this registry is minimal and solely consists of time. Any future results may be beneficial for subsequent patients.

Participation or refusal to participate in the registry will neither have consequences for their treatment.

## **1. INTRODUCTION AND RATIONALE**

The thoracic outlet syndrome (TOS) refers to a series of signs and symptoms caused by compression of the neurovascular bundle in the thoracic outlet. The thoracic outlet is the anatomical space through which the brachial plexus, subclavian artery and subclavian vein pass from the thorax to the arm. We can distinguish three TOS forms based on the compressed structures. Neurogenic thoracic outlet syndrome (nTOS) is the most common form and accounts for approximately 90-95% of all TOS patients, whereas venous TOS (vTOS) (5-10%) and arterial TOS (aTOS) (<1%) are less common.(1)

All three TOS forms can be treated conservatively and invasively. However, very little is known regarding risk factors, optimal treatment strategies, and long-term treatment results such as symptom free survival and vascular patency.(2-12) Consequently, setting up a registry can provide a way to collect high quality long term follow-up data for future research. By initiating this new registry, we eventually aim to create an international cooperation linking expert centres on TOS.

## 2. OBJECTIVES

**Primary Objective:** To create a registry that can be used for future research on optimising diagnostic protocols, treatment strategies, improving symptom-free survival and optimising patient follow-up among all three forms of TOS patients.

## 3. REGISTRY DESIGN

This is a monocenter longitudinal observational registry. The duration is for an indefinite amount of time.

## 4. REGISTRY POPULATION

### 4.1 Population (base)

Adult patients (aged 18 years and older), who are diagnosed with TOS and are currently being treated or have been treated at the UMCU in the Netherlands, are eligible for this registry. In addition, patients with a primary upper extremity deep venous thrombosis without a clear vTOS compression will also be eligible.

### 4.2 Inclusion criteria

In order to be included in this registry, a subject must meet all of the following criteria:

- A positive diagnosis for nTOS, or aTOS;
- Primary upper extremity deep vein thrombosis, including vTOS;
- Aged 18 years and older;
- Signed informed consent from patients and/or their legal representative

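### Section 4.2 requires two alternative diagnoses together, which contradicts the population in section 4.1 and the Summary

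*Protocol*

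**What the plan says.** Section 4.2 (Inclusion criteria) introduces its list with "In order to be included in this registry, a subject must meet all of the following criteria". Four bullets follow. The first is "A positive diagnosis for nTOS, or aTOS" and the second is "Primary upper extremity deep vein thrombosis, including vTOS". The other two concern adult age and signed consent, which a legal representative may give.

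Section 4.1 (Population) describes the cohort differently. Adults "who are diagnosed with TOS and are currently being treated or have been treated at the UMCU in the Netherlands, are eligible for this registry". It then opens a further route: "In addition, patients with a primary upper extremity deep venous thrombosis without a clear vTOS compression will also be eligible". The Summary agrees with 4.1: "All adult patients diagnosed with aTOS, nTOS or vTOS who are currently being treated or have been treated" at the centre are eligible, and primary UEDVT without clear venous compression is added.

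Section 2 sets the objective for all three forms of TOS. Section 6.2 has every patient with a positive TOS diagnosis informed about the registry. Section 4.3 excludes secondary UEDVT and people unwilling to consent, and says nothing on how the inclusion bullets combine.

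**The concern.** The first two bullets of 4.2 describe different patients: those with neurogenic or arterial TOS (nTOS, aTOS), and those with primary UEDVT or venous TOS (vTOS). The lead-in makes both compulsory. The author used an alternative inside the first bullet but not between the first and second, so nothing in the list turns them into alternatives.

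Section 4.2 is the list that staff would check before enrolment. The registry has no planned end (sections 3 and 7.4), is meant to grow into an international database (sections 1 and 7.4), and is to serve research questions not yet known (Summary). Followed exactly, the list would turn away most of the patients for whom the registry was set up. If it is reinterpreted informally, the protocol leaves no written rule by which a later user could reconstruct who was eligible.

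A second, smaller difficulty lies in the wording on vTOS. The Summary and section 1 classify TOS by the compressed structure, but 4.2 names vTOS only within a bullet on thrombosis.

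**Working it through.** The registry states no sample size or hypothesis test, so there is no figure to reproduce. The check is a logical reading of 4.2 for each type of patient, assuming age and consent are met and no exclusion applies.

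Let A = nTOS or aTOS (first bullet) and B = primary UEDVT, including vTOS (second bullet).

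- Section 4.2 as written: A **and** B.
- Section 4.1 and the Summary: nTOS, aTOS, vTOS **or** primary UEDVT without clear vTOS compression.

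| Patient has | A | B | 4.2 as written | A or B | 4.1 and Summary |
|---|---|---|---|---|---|
| nTOS only | yes | no | not eligible | eligible | eligible |
| aTOS only | yes | no | not eligible | eligible | eligible |
| vTOS only, with thrombosis | no | yes | not eligible | eligible | eligible |
| vTOS only, without thrombosis | no | unclear | not eligible | unclear | eligible |
| Primary UEDVT without clear vTOS compression, no TOS | no | yes | not eligible | eligible | eligible |
| nTOS or aTOS, plus primary UEDVT (with or without vTOS) | yes | yes | eligible | eligible | eligible |

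As written, 4.2 admits only the last row. Joining the bullets by *or* restores every row except vTOS without thrombosis, where the answer depends on how the second bullet is read.

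**Can the overlap be sized?** Section 1 says that nTOS "accounts for approximately 90-95% of all TOS patients, whereas venous TOS (vTOS) (5-10%) and arterial TOS (aTOS) (<1%) are less common". Two illustrations follow, each resting on an assumption that the protocol does not make.

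- If the three forms never coexist and no nTOS or aTOS patient has a separate primary UEDVT, A and B never hold together, and 0% of TOS patients are eligible.
- If every vTOS patient also has nTOS or aTOS, all vTOS counts under B, and there is no other primary UEDVT among nTOS and aTOS patients, then 5-10% of TOS patients are eligible.

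Neither gives a bound. B also covers primary UEDVT without vTOS, and the protocol does not say how often this occurs in nTOS or aTOS patients. The section 1 shares also come from a cited source and are not the case mix of this centre.

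**The case against.** The strongest answer is that nobody would apply 4.2 literally. The Summary and sections 2, 4.1 and 6.2 all point to the same intended population, and the literal rule would defeat the registry's purpose. This is a single-centre observational registry of standard care, and each later study needs its own application to the ethics committee, in which it can define its own analysis population. This stands as far as intent goes: the target population is not wrong, and there is no evidence that anyone has been wrongly refused. It does not repair the list, because no other section says that the two bullets are alternatives.

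Three stronger readings are tempting, and the protocol does not support them.

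- A reader might infer that the eligible set cannot exceed the 5-10% share of vTOS. It does not follow, because the second bullet is wider than vTOS.
- A reader might infer that vTOS without thrombosis is definitely shut out of 4.2 even once the bullets are joined by *or*. The second bullet does name vTOS, and its wording can be taken as listing vTOS as an admitted diagnosis in its own right. Section 4.3 does not exclude such patients. The text is ambiguous; it is not a settled exclusion.
- A reader might infer that the vTOS group will be selected on severity. The protocol does not describe case-by-case inclusion, does not equate thrombosis with severity, and does not mention or size a vTOS group without thrombosis.

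**Conclusion.** The contradiction is real. Applied exactly, 4.2 makes patients with nTOS alone, aTOS alone, vTOS alone or primary UEDVT alone ineligible, and these are the patients whom 4.1 and the Summary admit. The conclusion needs only the plain reading of the lead-in and the first two bullets, and no prevalence figure. How many patients would remain eligible cannot be derived from the protocol.

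This is a drafting error in the operative eligibility list, and the intended population can be inferred from the rest of the document. It should be corrected because the list is the entry rule for an open-ended registry. Whether vTOS without thrombosis is meant to enter is a separate ambiguity, which changing the connective alone would leave open.

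**What to change.** Reword section 4.2 so that a subject must satisfy all of the following:

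1. At least one diagnosis: nTOS; aTOS; vTOS; or primary UEDVT without clear vTOS compression.
2. Current or past treatment at the centre, as 4.1 has it. Section 4.1 attaches this condition to TOS patients and does not repeat it in its sentence on UEDVT, so the new text should make plain that it covers both.
3. The age bullet, unchanged.
4. The consent bullet, unchanged, including its provision for a legal representative.

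State expressly whether vTOS without thrombosis is included. Section 4.1 and the Summary admit vTOS with no condition of thrombosis, so if the sponsor intends otherwise, those two sections need changing as well.

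Match any eligibility check in the electronic case report form to the new text. Section 7.1 already ties changes to that form to a protocol amendment, so one amendment serves both. The cost is one paragraph and one form check, with no added procedures and no change to the population that 4.1 and the Summary describe.

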### 4.3 Exclusion criteria

A potential subject who meets any of the following criteria will be excluded from participation in this registry:

- Secondary upper extremity deep venous thrombosis;
- Individuals who are unwilling to sign complete or partial informed consent.

## **5. METHODS**

### **5.1 Parameters/endpoints**

#### **5.1.1 Main parameter/endpoint**

The main parameters of interest include, but are not limited to:

- Patient and treatment characteristics
- Symptom-free survival
- Vascular patency
- Treatment related complications
- Health-related Quality of Life (EQ-5D-5L) and Functional Disability questionnaire (Quick-DASH) sent at the time of inclusion and then after 1, 2, 5 years and then every 5 years.

The full list of parameters is presented in appendix 1. Depending on new insights on TOS these endpoints may be altered and updated.

### **5.2 Registry procedures**

A patient information form (PIF) will be provided to the participant as well as verbal information by the local principal investigator at the first hospital visit. In addition, a written, dated, and signed broad consent form will be obtained by the participant and local principal investigator. After obtaining broad consent, each participant is assigned a unique study ID. Consequently, all relevant clinical information will be extracted from the electronic health records (EHRs) and entered in the register's database in Castor EDC by members of the research team. The above mentioned questionnaires (see 5.1.1.) will be automatically sent via Castor by e-mail at set time points, namely at the time of inclusion, 1, 2 and 5 years after inclusion and then every 5 years. It will take the participant approximately 15 minutes to complete the self-administered questionnaires. In case of no response, patients will receive a reminder after 14 days to complete the questionnaire. The treatment, additional diagnostic imaging and laboratory test that subjects will undergo are standard care and indicated by the treating physician in accordance with the latest guidelines and will not be influenced by participation in the registry.

### **5.3 Withdrawal of individual subjects**

Subjects can leave the registry at any time for any reason if they wish to do so without any consequences. They can submit the withdrawal form that is included in the patient information. Subjects can either choose to exclude their data from further research or to allow the data that was collected before withdrawal to be used in further research. If a subject chooses to exclude their data from further research this data will be destroyed.

### **5.3.1 Specific criteria for withdrawal (if applicable)**

Participation is voluntarily, the patient decides whether to participate or not.

### **5.4 Replacement of individual subjects after withdrawal**

As it concerns a growing group of participants, no participants will be replaced.

### **5.5 Follow-up of subjects withdrawn from treatment**

There will be no follow-up of subjects that are withdrawn from the registry and it has no consequences for any further treatment.

## **6. ETHICAL CONSIDERATIONS**

### **6.1 Regulation statement**

The registry will be designed and implemented according to 'gedragscode gezondheidsonderzoek' and 'toetsingscriteria eenvormige toetsing' that consist of the laws: 'WGBO (Wet op de Geneeskundige BehandelingsOvereenkomst)' and Good Data Protection Regulation (GDPR) (Dutch: Algemene Verordening Gegevensbescherming (AVG)).

### **6.2 Recruitment and consent**

All patients with suspected TOS are discussed in a multidisciplinary team of radiologists, vascular surgeons and internal vascular medicine specialists where the treatment strategy is determined. All patients with a positive diagnosis of TOS will be informed about the registry by their treating physician at their first hospital visit, subsequently they are presented the patient information form (PIF) and informed consent (IC) form. At their next physical visit to the hospital, at least 24 hours later, the patient is presented the opportunity to ask any questions about the registry. If the patient wishes to participate in the registry, informed consent is obtained by the local principal investigator (PI) and the IC form is signed by the patient and PI. The participant is presented a copy of the IC form. The IC forms are stored at a secured location at the department of vascular surgery in the UMCU. Recruitment and consent of the patient is recorded in the electronic health record.

## **7. ADMINISTRATIVE ASPECTS, PRIVACY INCIDENTS AND END OF REGISTRY REPORT**

### **7.1 Handling and storage of data and documents**

Data will be handled confidentially and will be coded according to the order of entry. Confidentiality will be maintained at all times, participant information will not be disclosed to third parties. For this registry, only eligible patients admitted or with an appointment at the UMCU will be asked by their treating physician to participate. Direct identifiable—personal data from these patients will be recorded in an Excel file and stored in a secure research folder from the TOS registry on the UMCU network drive. This is for an overview of which patients are asked to participate.

After given broad consent, patients will also be registered in our electronic health record (EHR, HiX). The original signed broad consent forms will be kept in a binder in a locked closet in a locked room at the department of vascular surgery. Subsequently, the participant is assigned a unique study ID generated by Castor EDC. The key file containing the combination of the participants unique study ID and its personal information (name and date of birth) will be stored at a secured location at the UMCU network drive, only the local principal investigator has access for identification purpose. All relevant clinical information will be manually extracted from the EHR's and entered by the local principal investigator into an electronic Case Report Form (eCRF) the UMCU endorsed system Castor EDC. Castor EDC is a browser-based, metadata-driven EDC software solution and workflow methodology for building and managing online databases. The eCRF contains data items as specified in this research protocol. Modification of the eCRF will be made only if deemed necessary and in accordance with an amendment to the research protocol. Access to the eCRF is password protected and specific roles are assigned (e.g. study coordinator, investigator, etc.). In addition, the upper mentioned questionnaires (see paragraphs 5.1 and 5.2) will be sent automatically to the participants at set times via an email link using Castor. Only UMCU researchers will have access to all the collected data in Castor.

When needed for future research, the research data will be extracted and stored in the file format(s) SPSS and/or R in a secure research folder. The research analyst, data manager, researcher, physician and principal investigator(s) will get access to the research data. To be able to reproduce the research findings and to help future users to understand and reuse the data all changes made to the raw data and all steps taken in the analysis will be documented in syntaxes and by using new versions of the database. The original database will not be altered and is stored on the research network disc of my division. The research

data will be archived on the research network disc of the division for 15 years after the registry has ended. More details can be found in the datamanagement plan: <https://dmponline.dcc.ac.uk/plans/69559>

## **7.2 Ethical Committee**

Any research that will be conducted with (parts of) the data from this registry will be submitted to the METC. Data will only be used for future research after a positive advice or 'niet-WMO verklaring' from the METC.

## **7.3 Privacy incidents**

The person that notices a privacy incident, needs to report this immediately to the Central Coordinator of Information security (Dutch: Centrale Coördinator Informatiebeveiliging) stating the following information: contact information of reporter, description of the incident (including an indication of the impact on privacy) and actions that have been taken to control damage. A privacy incident is a security breach that can lead to loss or unlawful processing of personal data.

## **7.4 End of registry report**

The coordinating investigator will notify the dHS Research Office (DHS [contact] and [contact]) of the end of the registry. The goal of this registry is to create an international database that is unique in both size and long term follow-up. Hence we cannot define an specific end of this study.

## **7.5 Publications**

Researchers will publish results from research with data from this registry in public. Researchers are responsible for the completeness and accuracy of publications. Researchers will comply with the guidelines for ethical publication of results. If (international) co-operators of this registry want to use registry data for publication, data transfer agreements, nWMO study agreements contracts regarding intellectual property rights will be used. Patients will be informed on the international nature of this registry in the PIF.

The contributors involved are nationally and internationally recognised for their work in this registry. In case a large number of individual authors is not allowed by the guidelines of the journal, all individual contributors will appear in PubMed.

Before submission of a manuscript, every principal investigator and co-investigator will be sent the draft manuscript. The principal (co)investigator will provide the first author with her/his comments within 28 days. Also, he/she indicated whether a co-authorship is

appreciated. If no response has been obtained after 28 days, the principal (co)investigator is assumed not be interested in the manuscript and removed from the author list. Mentioning of the principal (co) investigators in the participating center/participant list remains, unless explicitly indicated that this should not be done.

